### Ethics Approval

This research was reviewed and approved by the Arizona State University Institutional Review Board (STUDY00014710) on 11/9/2021. This study has also been registered at ClinicalTrials.gov NCT05217602. Participants will provide consent electronically and will be emailed a copy of the consent form for their records. Participants can withdraw from the study at any time without penalty and request that their data be removed from the analysis. The data collected by the research team will be stored on a password-protected cloud-based secure server. All data retrieved from the questionnaires will be deidentified (kept separate from any personal identifying information, including consent forms). The questionnaire data will only be linked to individual participants via the assigned study ID numbers. Only anonymous aggregated data regarding app use during the 8-week study and an additional 8-week postintervention observation period will be retrieved from the Calm informatics team. All the participants will be compensated US $20 in electronic gift cards for completing the 3 web-based surveys (ie, baseline, postintervention, and follow-up surveys). Participants in either the NTCI or TCI groups will also be eligible to win up to 4 incentives during the intervention period, in addition to a US $20 gift card as compensation for completing all 3 web-based surveys.

## Results

Recruitment for this study was expected to occur between March 2022 and May 2022. Data collection is expected to be completed by October 2022. The results from this study will be available within 12 months of the final data collection date, which will be sometime between late 2022 and early 2023. The findings of this research will be disseminated using various methods, including peer-reviewed journals, academic conferences, and other verbal and digital communication platforms.

## Discussion

### Overview

Mobile meditation apps can be an effective and feasible way to deliver mindfulness meditation interventions. However, low intervention adherence over time limits the long-term potential of these apps. This study aims to address this critical issue by testing a combination of behavioral intervention strategies to determine the optimal combined strategy for establishing and maintaining meditation habits with a mobile app. To accomplish this, we have three specific aims: (1) assess study group differences in adherence to the daily meditation prescription during the 8-week intervention, (2) estimate study group differences in adherence maintenance over the 8-week postintervention observation period, and (3) investigate the role of anchoring performance during the intervention on the participants’ ability to maintain their meditation app adherence during the postintervention observation period.

This study will make important contributions to mHealth and behavior change research. First, the results of this study will improve future app-based interventions by identifying the most effective strategies for establishing and maintaining adherence to a mobile app, adding to the sparse body of literature on adherence to app-based interventions, particularly those for mindfulness meditation. Current research on app-based interventions is limited by poor adherence, and improving adherence is necessary to understand the full potential of app-based interventions for promoting health behavior change as well as the associated benefits from these health apps. This is particularly important for health behaviors such as mindfulness meditation, which requires maintaining a long-term practice to experience the maximum physical and mental health benefits. Second, this study will assess adherence by using objective app use data. Previous studies examining adherence in app-based interventions have found significant discrepancies between self-reported (eg, retrospective, daily diaries) and objective measures of adherence, as self-report measures are subject to more biases such as recall or response bias [115]. Testing strategies for maintaining objective measures of app-based intervention adherence will provide more rigorous evidence that will help to better understand the habit formation process in this setting. Finally, this research will make important contributions to the behavior change literature, in which existing interventions in the psychology and behavioral economics literature have largely been unsuccessful in maintaining behavior changes after interventions. By combining the anchoring habit formation strategy from psychology with behavioral economics–based incentives (ie, in-kind prizes awarded for short-term behaviors), this study will provide important evidence for a novel combined approach that may be more successful in maintaining behavior changes and will help improve our understanding of the habit formation process.

Several potential limitations of this study must also be addressed. First, the 8-week intervention period may not be sufficient to develop a strong and long-lasting meditation habit. Similarly, the 8-week intervention and 8-week postintervention periods may not be long enough to adequately assess our primary and secondary outcomes. Future research should plan to assess adherence and our secondary outcomes over longer periods to better understand the long-term effectiveness of these strategies. Another limitation to consider is the likely demographic characteristics of the recruited sample. Previous studies using Calm have reported samples that consisted of predominantly individuals who are White, female, and have bachelor’s degrees or higher qualification [116,117]. As a result, we anticipate having difficulty recruiting a diverse sample, which will limit the generalizability of our findings. In addition, studying the meditation app behavior of paid subscribers to a meditation app may not be generalizable to the general population. We plan to address this limitation by using a stratified randomization method to ensure that each study group has equal representation across racial and ethnic groups. Finally, it is possible that the incentives (ie, Calm prizes) provided to the NTCI and TCI groups during the intervention period may not be incentivizing to participants. We will test this by comparing the NTCI and TCI groups with the control group and by examining which items were most commonly chosen by eligible participants, and we will publish the results of these analyses to help determine the magnitude of incentives in future incentive-based meditation studies.

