Different types of self-monitoring messages may also influence anchoring plan adherence [86-88]. Self-monitoring has been cited as an important facilitator of behavior change and habit formation [74], and many existing mHealth apps have incorporated self-monitoring features to improve and sustain user engagement [89-91]. In addition, existing interventions have successfully used prompts either alone or in combination with other strategies to support health behavior change [92,93]. According to Michie et al [94], there are 2 types of self-monitoring: self-monitoring of behavior and self-monitoring of behavior outcomes. Messages that focus on self-monitoring of a target behavior (eg, number of completed meditation sessions during the past week and changes in the number of completed meditation sessions over time) may increase self-efficacy for a behavior by helping individuals visualize their effort investment and compliance with their behavioral goals [74]. Self-monitoring of behavior also helps individuals build self-regulatory skills [95], which may be particularly useful during the “learning phase” of the habit formation process [46]. Alternatively, messages that focus on self-monitoring of the outcomes associated with the meditation practice may increase the salience of both the immediate and long-term benefits of meditation practice, which may not be as clear from meditation practice alone [96,97]. In fact, our previous work on the Calm app’s self-monitoring mood check-in feature (ie, assessing and documenting mood before or after meditation practice) found that using mood check-ins was associated with increased meditation engagement, particularly among inactive subscribers [96]. As the mental health benefits of meditation are not immediately observable, messages that focus on the self-monitoring of outcomes of behaviors (ie, mood check-ins) may be a more effective way to reinforce participants’ adherence to the ≥10 minute-per-day meditation prescription than messages that focus on self-monitoring of behavior, which can only provide an indirect signal of participants’ mental health benefits. By varying the type of self-monitoring messages (ie, behavior or outcomes of behavior) between intervention study groups, we will be able to test the following hypothesis:

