### Study Design

This study will use a 5-arm, parallel, partially blinded (participants only) randomized controlled design. After completing a web-based eligibility survey, the participants will be randomized into 1 of the 5 study groups. Stratified randomization methods will be used to ensure that race and ethnicity (ie, Hispanic) are equally represented across study groups. The 5 study groups include a control group that will use the anchoring plan to form a meditation habit with Calm and then receive no additional intervention supports, while the 4 intervention groups will also use the anchoring plan in combination with 1 of the 2 different types of self-monitoring messages and 1 of the 2 different forms of incentives. Participants in the 4 intervention groups will also be eligible for an in-kind reward (eg, Calm t-shirt, Calm tote bag, or Calm water bottle; all gifts have a retail value of roughly US $25 but a wholesale cost of US $5) conditional on either completing ≥10 minutes of meditation at any time of day on at least 8 days over a 2-week period (NTCIs) or completing ≥10 minutes of meditation within a 2-hour window around the time their chosen anchor typically occurs during the day (ie, anchor time1 hour) on at least 8 days over a 2-week period (TCIs). All additional interventions to support adherence to the anchoring plan will be delivered for 8 weeks; thus, participants are eligible to win up to 4 in-kind incentives during the intervention period. Participants within the intervention groups will also be randomly assigned to receive either messages that focus on self-monitoring of behavior (eg, “You completed a meditation session using your Calm app on at least 8 days during the past 2 weeks”) or messages that focus on self-monitoring of outcomes of behavior (eg, “We encourage you to continue using the ‘How Are You Feeling?’ check-in feature after completing your meditation sessions”). The “How Are You Feeling?” check-in feature is an existing feature available to all users of the Calm app that allows users to record their current mood state (eg, happy, sad, or anxious). The fractional factorial study design is shown in Table 1.

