#### Introductory Video

Immediately following the web-based surveys, participants will then watch 1 of 3 brief 5-minute introductory videos that will vary slightly based on their experimental conditions. All 3 videos will contain background information on the benefits of mindfulness meditation and habit formation (eg, previous research and theory); a sample anchoring plan (eg, “After [insert behavior here], I will meditate for 10 minutes”); a study timeline (ie, baseline assessment, 8-week intervention period, follow-up assessment, 8-week postintervention period, and second follow-up assessment); and compensation information for completing the 3 web-based surveys (US $20 gift card). In addition to these foundation elements, participants in the NTCI and TCI groups will be told in the video that they are eligible for incentives every 2 weeks during the 8-week intervention period conditional on either meditating at any time (NTCIs) or meditating using their anchoring plan (TCIs). The video for the usual Calm condition will only include the foundation elements mentioned previously, with no mention of incentives or personalized feedback messages. Information in all 3 videos will be presented by a member of the study team using both written and spoken texts. Participants in the NTCI and TCI groups will also receive instructions regarding prize eligibility as detailed in the *Study Design* section.

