#### Intervention, Postintervention, and Follow-up Surveys

The 8-week intervention period will begin once the participants complete the baseline assessment and anchoring plan worksheet. All the participants will be asked to meditate for ≥10 minutes every day during the intervention period. Every 2 weeks, participant use data will be checked to determine incentive eligibility for participants in the NTCI and TCI groups. Every week, all the participants will also receive a text message from the study team as a reminder to continue meditating using their chosen anchor. In addition, participants in the BM group will receive a message focused on self-monitoring of their meditation behavior every 2 weeks that informs participants of the number of ≥10-minute meditations they completed during the past 2 weeks. Participants in the self-monitoring of outcomes of behavior messages groups will receive a message focused on self-monitoring of outcomes of their meditation behavior (ie, mood tracking) every 2 weeks that encourages the participants to keep track of their mood using the “How Are You Feeling?” feature in the Calm app. After 8 weeks, participants will be emailed a link to complete the first of the 2 follow-up surveys. These surveys will assess any improvements in the secondary outcome measures assessed at baseline, as well as their satisfaction with both the Calm app itself and the interventions. Following the completion of the 8-week intervention period and the week-8 follow-up survey, participants will be asked to continue using their anchors to strengthen their meditation habits during the 8-week postintervention observation period. However, unlike in the intervention period, participants in all intervention groups will no longer receive weekly reminders, biweekly self-monitoring messages, or incentives during the postintervention period. Participants will then be contacted at week 16 to complete the second follow-up survey to assess changes in the secondary outcome measures at week 16.

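### Comparing the incentive arms with control cannot show whether the prizes motivate, because every incentive arm also receives self-monitoring messages and control receives neither

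*Protocol article*

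**What the plan says.** The limitations part of the Discussion (Overview) raises the possibility that the prizes "may not be incentivizing to participants". It answers: "We will test this by comparing the NTCI and TCI groups with the control group". It adds a look at which items eligible participants chose, and says the results will help to set the size of incentives in later studies.

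Methods, Study Design, describes the arms. Control is "a control group that will use the anchoring plan to form a meditation habit with Calm and then receive no additional intervention supports". The four intervention groups use the anchoring plan "in combination with 1 of the 2 different types of self-monitoring messages and 1 of the 2 different forms of incentives". Table 1 shows the same allocation, and the Introductory Video section says that the control video is shown "with no mention of incentives or personalized feedback messages".

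The Introduction gives the messages a role of their own: "Different types of self-monitoring messages may also influence anchoring plan adherence". The weekly anchor reminder is separate from these: "all the participants will also receive a text message from the study team as a reminder". It reaches control too, so it does not distinguish the arms.

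**The concern.** The sentence promises a test of one component, the prizes, from a comparison in which two components change together. Whatever separates an NTCI or TCI arm from control is the joint effect of a self-monitoring message and an incentive.

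The main risk is in reading a positive result. A difference from control would be taken as evidence that the prizes work and carried into the choice of incentive size in later trials, even if the messages produced all of it. A null result is also not clean evidence about the prizes, although it misleads only if the messages lower adherence. Incentive size is not varied either: Study Design gives all gifts a retail value of roughly US $25.

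**Working it through.** **The plan's own figure.** Sample Size gives 88 per group after 20% attrition (111 × 0.8 = 88.8), Cohen h = 0.43 and power 0.82. With two-sided alpha 0.05 (assumed, as the article does not state it), power = Φ(h√(n/2) − 1.96) = Φ(0.43 × √44 − 1.96) = Φ(0.892) = 0.81. This agrees with the stated figure. It concerns one arm against another and does not bear on identification.

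**What Table 1 identifies.** AP is 1 in every row and acts as the intercept.

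| Arm | BM | OM | NTCI | TCI | BM+OM | NTCI+TCI |
|---|---|---|---|---|---|---|
| Control | 0 | 0 | 0 | 0 | 0 | 0 |
| Treatment 1 | 1 | 0 | 1 | 0 | 1 | 1 |
| Treatment 2 | 0 | 1 | 1 | 0 | 1 | 1 |
| Treatment 3 | 1 | 0 | 0 | 1 | 1 | 1 |
| Treatment 4 | 0 | 1 | 0 | 1 | 1 | 1 |

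The last two columns are identical: receiving any message and receiving any incentive are the same variable. The five-column matrix (AP, BM, OM, NTCI, TCI) has rank 4. A contrast is estimable only if it lies in the row space of that matrix:

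- Not estimable: NTCI v none, TCI v none, their average, BM v none, OM v none.
- Estimable: TCI − NTCI, OM − BM, NTCI + average message effect, TCI + average message effect.

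The last two estimable quantities are what the comparison with control delivers. The logistic models in the Data Analysis Plan have one indicator per arm, so each coefficient carries a message type and an incentive type. The alias lies in the design columns and holds equally on the logit scale.

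**Two opposite truths, same data.** Take a control rate of 10%.

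- Prizes add 18 points, messages add 0: arm rates 10, 28, 28, 28, 28%.
- Prizes add 0, messages add 18 points: arm rates 10, 28, 28, 28, 28%.

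No sample size separates them.

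**How often inert prizes would appear to work.** Assume the prizes do nothing and the messages alone raise regularity from 15% to 23% or 27%. The 15% is the week-8 figure in Sample Size, and week 8 closes the period in which prizes are offered. The 23% and 27% are assumptions.

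- h = 2·arcsin√p₂ − 2·arcsin√p₁: h(0.15, 0.23) = 0.205 and h(0.15, 0.27) = 0.297.
- Effective n = n₁n₂/(n₁+n₂), and probability of significance = Φ(h√n_eff − 1.96).

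| Comparison with control (88) | n_eff | 15% → 23% | 15% → 27% |
|---|---|---|---|
| All four arms, 352 | 88×352/440 = 70.4 | 0.41 | 0.70 |
| NTCI or TCI pair, 176 | 88×176/264 = 58.7 | 0.35 | 0.62 |
| One arm, 88 | 88×88/176 = 44 | 0.27 | 0.50 |

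**The case against.** The aliasing itself cannot be disputed. The best case for leaving the text alone rests on the following points.

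- **Other evidence bears on the prizes.** TCI v NTCI is balanced on message type and planned under Hypothesis 2. If TCI participants meditate in the anchor window more often, they are responding to the reward rule, which suggests that the prizes matter. This stands as indirect evidence, but it compares two reward rules and is not the comparison the sentence names.
- **A null is partly informative.** The stated worry is that prizes may not work, and no difference from control would point that way unless the messages do harm, which the Introduction does not expect. This stands. The serious risk is in the positive reading.
- **Item choice and survey items are also planned.** Item choice is seen only in those who earned a prize and shows preference among prizes, not an effect on meditation. The Satisfaction section does ask intervention participants how motivated they were by the incentives. That is useful, but it is self-report and not a between-arm test.
- **Nothing central depends on the sentence.** Hypotheses 1 and 2 and the sample size do not use it, and the Data Analysis Plan labels each arm openly as message plus incentive. This stands and limits the consequence to one claim.
- **The probabilities are illustrative.** They are smaller if arms are not pooled, as the table shows, and the week-16 base rate is below 10%. This is correct, but the finding does not depend on them.

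**Conclusion.** The concern holds. The effect of receiving any prize is completely aliased with the effect of receiving any self-monitoring message, so the comparison named in the Discussion cannot test whether the prizes are incentivizing. This follows from Table 1 alone, without distributional assumptions, and no separate analysis plan could repair it.

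The 41% and 70% figures illustrate the risk of misattribution. They rest on inert prizes, assumed message effects of 8 and 12 points on a 15% base, pooling of the four treated arms, and two-sided alpha 0.05. Comparing the package with control is legitimate. Attributing the difference to the prizes is not. TCI v NTCI and outcome v behavior messages are unaffected.

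**What to change.** Replace the sentence in the Discussion with a statement along these lines: comparisons of the intervention groups with control estimate the combined effect of self-monitoring messages and incentives over the anchoring plan with weekly reminders; the separate effect of receiving any incentive, or any self-monitoring message, is not identified by this design. List this among the limitations.

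Assess the prizes descriptively, using uptake by 2-week period and the planned week-8 items on incentive motivation. Restrict causal claims about components to TCI v NTCI and outcome v behavior messages, and drop the suggestion that the control comparison can guide incentive size.

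The cost is wording and one claim fewer. Testing the prizes themselves would need at least one arm with messages and no incentive. Under additivity that raises the rank to 5 and makes the incentive effects estimable, but at 111 per group it would take the target from 555 to 666. The wording change does not require it.

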### Conclusions

This study will contribute to an important gap in the literature by testing novel intervention approaches for establishing and maintaining adherence to app-based mindfulness meditation. We are using unique combinations of previously established intervention strategies from the psychology and behavioral economics literature to help participants better maintain adherence to an effective dose of meditation that can reduce stress. If successful, this study will identify an accessible and scalable stress self-management intervention to combat the ongoing stress epidemic in the United States.

## Appendix

Multimedia Appendix 1 Data analysis plan.

## Abbreviations

ISI: Insomnia Severity Index
mHealth: mobile health
NTCI: non–time-contingent incentive
PSS: Perceived Stress Scale
PTSD: posttraumatic stress disorder
SRHI: Self-report Habit Index
TCI: time-contingent incentive
